## Abstract

**Background:**

Acute interstitial nephritis (AIN) is an important and common cause of acute renal failure. There are no generally accepted guidelines for the treatment of AIN, due to the lack of prospective randomized trials. Since AIN is characterized by an enhanced immune response, immunosuppressive treatment could potentially improve prognosis by attenuating inflammation and subsequent fibrosis. Despite the limited evidence of effects of steroids and potential adverse effects, prednisolone is frequently used in the treatment of AIN and there is a strong need for clinical trials on the effects of immunosuppression, including steroids, in the treatment of AIN. We aimed to evaluate the effectiveness of prednisolone treatment in AIN, and hypothesized a positive effect of prednisolone treatment on renal function in AIN.

**Methods:**

The study is a randomized, controlled, prospective, open label multicenter study, including incident adult patients with biopsy proven AIN. Patients will be randomized 1:1 to one of 2 treatment regimens:
A.No prednisolone treatment (control group) andB.B) Oral prednisolone treatment staring with 60 mg daily tapered over 8 weeks.

One hundred ten patients (55 in each group) are planned to be included and followed for 1 year. Primary outcome is renal function estimated by eGFR 3 months after inclusion. Secondary outcomes are renal function after 12 months and need for renal replacement therapy and quality of life after 3 and 12 months. In addition, with-in prednisolone group analysis are performed to estimate the importance of treatment delay. Exploratory analyses include analysis of biomarkers in urine and plasma and the evaluation of these biomarkers in relation to renal prognosis and re-evaluation of renal biopsies to identify possible renal prognostic factors.

**Discussion:**

Strengths and possible limitations in the design are evaluated. The study will provide important information on the effects of prednisolone treatment in AIN and as well as prognostic information relevant for future use of biomarkers and histology. Ultimately, this would lead to improved and evidence based clinical guidelines for the treatment of AIN.

**Trial registration:**

ClinicalTrials.gov identifier NCT04376216 (Retrospectively registered on May 6, 2020).

## Background

Acute renal failure is associated with greatly increased mortality and morbidity irrespective of its cause [1, 2]. Acute interstitial nephritis (AIN) is an important and common cause of acute renal failure and occurs in 13–27% of renal biopsies performed in acute renal failure requiring dialysis in 40% of cases [3–6]. Histologically AIN is characterized by peritubular inflammation while glomeruli and vessels are typically spared [7]. Although some patients recover renal function completely, as many as 30–70% do not fully regain renal function leading to chronic kidney disease (CKD) [6, 8–14]. CKD is associated with increased morbidity and mortality. Two recent studies suggested that the risk of end stage renal disease requiring dialysis after biopsy proven AIN is 5–7% [6, 13].

In addition to renal failure AIN may present with joint pain (45%), fever (36%), skin rash (22%), eosinophilia (35%), microscopic hematuria (67%), macroscopic hematuria (5%), leukocyturia (82%), non-nephrotic proteinuria (93%), nephrotic proteinuria (3%) and nephrotic syndrome (1%) [15]. AIN can be subdivided in 3 categories based on the precipitating cause: drug induced (75%), infection (5–10%) or autoimmune diseases (15–20%) [5, 7, 16–18]. The pathophysiological mechanisms leading to renal inflammation in AIN are not fully clarified. Fibrotic changes can be observed 7–10 days after the beginning of the inflammatory process and if the triggering cause is not eliminated, the inflammation may proceed to interstitial fibrosis, tubular atrophy and chronic renal failure [19]. Studies have shown that macrophages, lymphocytes and activated tubular cells produce various cytokines that stimulate proliferation of fibroblast cells leading to fibrosis [20, 21]. Transforming growth factor-β1 (TGF-β1) promotes fibroblast activity in vitro and alters the phenotype of mesangial cells to a more fibroblast-like phenotype [22, 23]. Transgenetic mice overesxpressing TGF-β1 show increased renal fibrosis [24, 25]. Thus, TGF-β1 appears to play a central role in the development of renal fibrosis [26]. Bone morphogenetic protein-7 (BMP-7), on the other hand is a natural antagonist of TGF-β1 with anti-fibrotic and anti-inflammatory properties [26]. The roles of TGF-β1 and BMP-7 in AIN; however, have not been elucidated.

There are no generally accepted guidelines for the treatment of AIN [27], but normally this would include elimination of the precipitating cause and stimulus leading to renal inflammation. Since AIN is characterized by an enhanced immune response, immunosuppressive treatment could potentially improve prognosis by attenuating inflammation and subsequent fibrosis. Case series have suggested positive effects of steroid treatment, but only few larger, retrospective registry based studies have examined this [6, 8, 9, 12–14, 19, 28]. At present, only three retrospective studies with more than 100 patients have been published [29–31]. Muriithi and colleagues identified 133 cases with AIN, of which 95 were drug-induced [31, 32]. The study showed no difference in renal function after 1, 3 and 6 months when comparing 83 steroid-treated with 12 non-steroid-treated patients. In steroid-treated patients, a longer time from the onset of symptoms or biopsy to the initiation of steroid treatment was associated with inferior restoration of renal function. A retrospective, Scottish study including 171 cases of drug-induced AIN also failed to demonstrate an effect of steroid treatment on renal function after 12 months of follow-up [30]. As in the previous study, the steroid-treated (*n* = 124) had higher baseline creatinine levels. In contrast, a recent study from England including 187 patients showed a possible positive effect of steroid treatment [29]. After 24 months, eGFR was 42 ml/min in the steroid-treated group versus 24 ml/min in non-steroid-treated patients. In addition, there was a tendency towards fewer patients requiring of dialysis after 24 months among those treated with steroid. Baseline renal function was comparable among the steroid- and non-steroid-treated patients. Interestingly, a sub-analysis including only patients with drug-triggered AIN, i.e. excluding patients with autoimmune disease, did not show any significant effect of steroid treatment. This indicates that steroid treatment may only benefit patients with autoimmune related AIN. Retrospective studies are hampered by selection bias and there are no published, prospective, randomized studies evaluating the effects of steroids in AIN leaving the use of steroids in AIN controversial. Steroid treatment has several physical and mental adverse effects, such as diabetes mellitus, hypertension, cataract, osteoporosis and manic episodes and is associated with hyperlipidemia, obesity and osteonecrosis [33]. Despite the limited evidence of effects of steroids and potential adverse effects, prednisolone is frequently used in the treatment of AIN and there is a strong need for clinical trials on the effects of immunosuppression, including steroids, in the treatment of AIN.

The usefulness of biomarkers to diagnose and to define prognostic and therapeutic subgroups in AIN has not been extensively studied [34, 35]. Potentially useful biomarkers in plasma or urine include neutrophil gelatinase-associated lipocalin (NGAL), N-acetyl-beta-D-glucosaminidase (NAG), kidney injury marker 1 (KIM-1), tissue inhibitor of metalloproteinases-2 (TIMP-2), insulin-like growth factor-binding protein 7 (IGFBP7), interleukin 18 (IL-18) and monocyte chemotactic peptide-1 (MCP-1) [36–40]. In particular, Urinary NGAL excretion may be helpful for the diagnosis and to establish prognosis, while urinary MCP-1 excretion has been correlated with the degree of renal inflammation and edema in drug-induced AIN [40]. Alpha-1-microgolbulin (A1M) and Beta-2-macroglobulin (B2M) are low molecular weight proteins that are freely filtered in the glomeruli and reabsorbed in the proximal tubule [18]. Tubular damage leads to increased urinary excretion and both A1M and B2M may used to assess proximal tubule damage. So far these have been mostly studied in chronic hereditary forms of interstitial nephritis, such as Balkan nephropathy and tubulointerstitial nephritis with uveitis (TINU) [41–44]. Thus, further studies are needed to establish the potential value of biomarkers for the diagnosis and management of AIN.

### Hypotheses

This study will examine the following hypotheses:
Prednisolone treatment in AIN is associated with a higher eGFR 3 and 12 months after inclusion when compared to no prednisolone treatment.Prednisolone treatment in AIN is associated with a greater decline in plasma creatinine from inclusion to 3 and 12 months after when compared to no prednisolone treatment.Prednisolone treatment in AIN shortens the time to remission or partial remission when compared to no prednisolone treatment.Prednisolone treatment in AIN reduces the number of patients requiring renal replacement therapy when compared to no prednisolone treatment.A greater timespan from the presentation of AIN to the initiation of prednisolone treatment is associated with a lower eGFR 3 and 12 months after inclusion.

### Design

An investigator initiated, randomized, controlled, prospective, open label multicenter study, including incident adult patients with biopsy proven AIN. Patients will be randomized 1:1 to one of 2 treatment regimens:
A.No prednisolone treatment (control group)B.Oral prednisolone treatment tapered over 8 weeks.

### Trial subjects

#### Recruitment

Patients are recruited consecutively at all Danish nephrology departments by local investigators.

#### Inclusion criteria

Clinical suspicion of AINRenal biopsy consistent with AINAge ≥ 18 yearsOne of following criteria:
○ Plasma creatinine > 120 μmol/L or○ Plasma creatinine increase > 30 μmol/L or > 50% when compared to baseline plasma creatinineInformed consent

#### Exclusion criteria

Inability to give informed consentImmunosuppressive treatment (including prednisolone) within 3 months prior to biopsyAny known systemic autoimmune diseasePrednisolone intolerancePregnancy or lactationActive cancer (except for basal cell carcinoma)Short life expectancy (< 6 months)CKD stage IV-VAIN secondary to or accompanied by glomerulonephritis, sarcoidosis or inherited interstitial renal diseasePrevious participation in this study

#### Withdrawal criteria

Development of any exclusion criterionWithdrawal of consent

#### Screening

All patients with a renal biopsy consistent with AIN are screened for participation and included in the screening log.

#### Randomization

Randomization is performed locally and electronically using REDCap (www.redcap.au.dk; Clinical Trial Unit, Aarhus University). Randomization is performed 1:1 in blocks of 6. Since only a few subjects are expected to be included each center, any center effects are considered insignificant. Neither clinicians nor patients are blinded to the study treatment group.

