### Statistics

The primary analysis will be performed as “intention to treat”, and the secondary analysis as “treated as”. Normally distributed variables are compared by unpaired t-test or one-way ANOVA. Repeated measures are analyzed using a general linear model (GLM). Comparable non-parametric tests are used in case of non-normally distributed variables. Both absolute and relative proportions are analyzed. Secondary end-points are analyzed as differences in absolute or relative proportions. Analysis of factors affecting the primary end-point will be performed using a GLM. Kaplan Meier curves will be used when appropriate e.g. in the evaluation of time to end stage renal failure. Any correlation between the primary end point and relevant secondary outcomes and outcomes form the exploratory analysis will be evaluated with appropriate adjustment for potential confounders.

Sample size was estimated for the primary outcome based on a clinical relevant 10 ml/min/1.73m^2^ difference in renal function (eGFR, CKD-EPI) between groups at 3 months, a standard deviation of 18 ml/min, a power of 0.80 and a significance level of 0.05. This showed that 51 patients should be included in each group. Anticipating dropouts, we estimate that 55 patients in each group are necessary and plan to randomize 110 patients.

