### Time schedule

The estimated trial duration is 8 years. The study was launched at the first centers on Sept 1, 2017. Since then, all 11 Danish nephrology centers have been enrolled caring for a population of approximately 4.7 million adults. Currently, 30 patients have been included, and 82 patients have been screened. Unpublished data suggest that approximately 15 patients per year is diagnosed with AIN in the Middle- and Southern regions of Denmark covering approximately 2.0 million adults. With the participation from all Danish nephrology centers, we expect recruitment to be feasible within the suggested time-frame.

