## Discussion

The study will provide important information on the effects of prednisolone treatment in AIN and as well as prognostic information relevant for future use of biomarkers and histology. Ultimately, this would lead to improved and evidence based clinical guidelines for the treatment of AIN. For years, treatment of AIN has been empirical, steered by clinical judgement and influenced by the results of retrospective studies hampered by selection bias. Many patients receive steroid treatment despite the lack of convincing evidence from randomized clinical trials. Treatment is driven by the potential long term benefits associated with the conservation of renal function, as chronic kidney disease has serious detrimental effects on morbidity and life expectancy. However, considering the potential serious adverse effects associated with steroids, the benefits of treatment should be better documented.

The prospective design with randomization to treatment should minimize selection bias for the patients who accept to participate. However, a selection prior or during recruitment is still a risk in this randomized design. Preferences by treating physicians may still determine and affect eligibility for participation in the trial. Thus, a systematic screening log of patient with renal biopsy proven AIN has been included allowing further characterization of the patients not included in the trial. This should enable us to identify if particular patient groups are withheld participation in the study. The study is a national Danish study and the Danish population is mainly of a Caucasian race and will therefor probably mainly include a Caucasian population. This will result in a uniform cohort but limit the generalizability to other populations with different racial composition.

Although we have no data to support this, it is likely that the threshold for renal biopsy in suspected AIN differs between centers depending on local practices, tradition and logistics. A direct consequence of this study may be that biopsy frequency increases to facilitate study participation. The requirement for a renal biopsy ensures the diagnosis of AIN and randomization minimize the risk of confounding due to different biopsy practices.

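### A single fixed block size of 6, published during recruitment of an open-label trial, makes some assignments foreseeable to anyone who can see a running block

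*Protocol article*

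**What the plan says.** The protocol article's Randomization section fixes the scheme in a few sentences. "Randomization is performed locally and electronically using REDCap". "Randomization is performed 1:1 in blocks of 6". "Neither clinicians nor patients are blinded to the study treatment group". On centres it says only: "Since only a few subjects are expected to be included each center, any center effects are considered insignificant". It gives no second block size and no stratification factor.

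The Time schedule section shows how far recruitment had come when the block size was printed: "Currently, 30 patients have been included, and 82 patients have been screened", and "all 11 Danish nephrology centers have been enrolled". The Statistics section gives the target: "we estimate that 55 patients in each group are necessary and plan to randomize 110 patients".

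The Discussion acknowledges that selection can still occur around recruitment: "Preferences by treating physicians may still determine and affect eligibility for participation in the trial". The response offered there is a screening log, intended to show which patients were not enrolled.

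**The concern.** In a 1:1 block of 6 each arm has exactly three places. Because treatment is open, past assignments are visible to those who treat the patients. Once one arm has used its three places, every remaining assignment in that block is known, and before that point the arm with more places left is the better guess. A reader of the article also knows that the size never changes.

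A recruiter with such foreknowledge could encourage or discourage a particular patient according to the arm expected next. The groups would then differ in prognosis before treatment starts. An intention-to-treat analysis does not remove that difference, nor does a laboratory endpoint such as eGFR. A screening log can describe the selection afterwards but does not prevent it. Protection against selection bias is the Discussion's stated reason for randomising, so it is worth closing the route if that is cheap.

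**Working it through.** **Inputs.** From the article: ratio 1:1 and block size 6 (Randomization); 11 centres and 30 patients included (Time schedule); 110 patients, 55 per arm, SD 18 and target difference 10 ml/min/1.73 m² (Statistics). Assumed: equal recruitment, 110/11 = 10 patients per centre; two-sided 5% tests. Allocations still to come at the time of writing: 110 − 30 = 80.

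**The plan's own figure.** The normal formula with difference 10, SD 18, two-sided alpha 0.05 and power 0.80 gives 51 per group, as stated. The sample size is not in dispute and block size does not affect it.

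**Step 1: a fully observed block of 6.** There are 20 equally likely orders of three A and three B. An assignment is certain when one arm is already full; otherwise the guess is the arm with more places left, and a tie counts one half.

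| Place in block | 1 | 2 | 3 | 4 | 5 | 6 | Sum |
|---|---|---|---|---|---|---|---|
| Probability certain | 0 | 0 | 0 | 0.1 | 0.4 | 1.0 | 1.5 |
| Probability guess correct | 0.5 | 0.6 | 0.6 | 0.7 | 0.7 | 1.0 | 4.1 |

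Certain: 1.5/6 = 25%. Guessed correctly: 4.1/6 = 68.3%. Over the 18 full blocks in 110 patients, 18 × 1.5 = 27 assignments would be certain.

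**Step 2: one list per centre, 10 patients each.** This is one full block plus the first four places of the next.
- Certain: (1.5 + 0.1)/10 = 16%.
- Guessed correctly: (4.1 + 0.5 + 0.6 + 0.6 + 0.7)/10 = 6.5/10 = 65%.

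**Step 3: one national list, each centre seeing only its own patients.** In simulation with patients spread at random over 11 centres, about 0.02% of assignments are certain, even if the centre knew where each block began. The guess stays near 50%: at place k of a block, the chance that the centre has at least one earlier patient in it is 1 − (10/11)^(k−1), which averages about 0.20 over the six places. When it has one or two, the guess is right 60% of the time (three or more is rare). That gives 0.50 + 0.20 × 0.10 = 52%.

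**Step 4: varying the block size, for someone who sees every allocation and knows the set of sizes (simulation).**

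| Sizes | Certain | Guess correct |
|---|---|---|
| 6 only | about 25% | 68% |
| 4, 6, 8 at random | about 2% | 68% |
| 4, 6 at random | about 5.5% | 69% |

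Varying the size removes most of the certain assignments but hardly changes the guess.

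**Step 5: illustration only.** Suppose there is no true effect and every recruiter shifts the prognosis of enrolled patients by v ml/min in the direction of the guessed arm. The false difference is 2v × (2 × proportion guessed − 1), and its standard error is 18 × √(2/55) = 3.43.

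| Setting | v | False difference | Two-sided type I error |
|---|---|---|---|
| Per-centre lists, 65% | 2.5 | 1.5 | about 7% |
| Per-centre lists, 65% | 5 | 3.0 | about 14% |
| Whole list visible, 68.3% | 5 | 3.7 | about 19% |

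The documents give no value for v, so these rows show a mechanism and do not estimate this trial's error rate.

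**The case against.** The strongest reply is that the harm depends on something the article does not state. The remark that centre effects can be ignored reads most naturally as the reason for not stratifying by centre, which means one list. Under that reading, a centre that sees only its own patients can foresee almost nothing (step 3). No section says that recruiting staff can see other centres' allocations. List structure and REDCap user rights are also details that an article may leave to the full protocol, so their absence is not a fault. All of this stands, and it is why the point is conditional.

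The plan also has more against selective enrolment than the screening log: consecutive recruitment, screening of all patients with a compatible biopsy, an approach to all such patients, electronic allocation and GCP monitoring. Accrual is thin as well. Thirty patients over 11 centres is 2.7 each, so under per-centre lists an average centre had not yet reached the fourth place, the first that can be certain. Over the planned 8 years the rate is 110/(11 × 8) = 1.25 patients per centre per year. These facts lower the practical risk. They do not remove it for a larger centre or for someone with a trial-wide view.

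Three stronger readings may tempt a reader, and the documents support none of them.
- That allocation has in fact been biased. Nothing shows this.
- That the same physicians screen, obtain consent and randomise. Recruitment is assigned to local investigators and randomisation is called local, but one person doing all three is an inference.
- That the Discussion admits physicians can foresee the arm. It speaks of who enters the trial, not of knowledge of the next assignment.

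**Conclusion.** The point holds as a conditional risk and a cheap improvement. A single block size of 6 in an open-label trial, published with about 80 allocations to come, lets anyone who can see a running block know 25% of assignments for certain and guess 68% correctly. With per-centre lists of about 10 patients, which assumes equal recruitment, this is 16% and 65%. With one national list and each centre seeing only its own patients, it is close to zero, and the text leans toward a single list. A reader might infer from step 5 that the trial's type I error is 14% or 19%. That does not follow, because those values rest on an assumed shift applied by all recruiters in the same direction. The article contains no contradiction or wrong figure here, and the sample size is unaffected.

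**What to change.** For the allocations that remain, have the Clinical Trial Unit load a list into REDCap with randomly varying block sizes, and neither disclose the sizes to investigators nor publish them while recruitment continues. Confirm at the same time that this is a single national list and that recruiting staff cannot see other centres' allocations or running totals. If that is already so, it is enough to say so and to stop disclosing the sizes.

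The two parts do different work. Varying the size takes certain assignments from about 25% to about 2% to 5.5%, so it removes most of them but not all, and it hardly lowers guessing by someone who sees every allocation. The single list with restricted view is what brings a centre's guess close to 50%.

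The cost is a new allocation table, possibly a change of user rights in the existing system, and a short amendment. The downside is a possible imbalance of a few patients overall and within centres.
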